**Full Trial Progression Criteria:**

We will progress to a full trial if we all our criteria below are classed as GREEN; if one or more is AMBER, we will investigate whether it is possible to make adjustments to the trial design to overcome any problems and, if that appears possible, progress to a full trial (including an assessment of the success of our adjustments in its internal pilot, where appropriate); if one or more is RED, we will not progress unless we can make the substantial amendments which would be necessary to make a full trial feasible.

1. Recruitment: GREEN: >=80% (n>=36) of target recruited; AMBER >=40 % (n=18-35)-< 80% of target recruited; RED <40% (n<18) of target recruited.
2. Retention: GREEN: >=80% of participants providing 16-week outcome data ; AMBER: >60%- <80% of

participants providing 16-week outcome data; RED: <60% of participants providing 16-week outcome data.

- 1. Adherence: GREEN>=75% adherence of participants attend at least 5 sessions of therapy, AMBER>=40% participants

attend at least 5 sessions of therapy; RED: <40% of participants attend at least 5 sessions of therapy (based on Jolley et al. 2015).

Assessment Measures

|  | **Procedures and Questionnaires** | **Mins** | **Baseline** | **16 Weeks Follow Up** | **28 Weeks Follow Up** |
| --- | --- | --- | --- | --- | --- |
|  | Demographics | 5 | X | As needed | As needed |
| **Psychosis Measures** | PANSS | 60 | X | X | X |
|  | PSYRATS | 15 | X | X | X |
|  | QPR | 5 | X | X | X |
| **Imagery** | Brief Imagery Interview  Visual Analogue Scales/MIPQ  Psychosis Imagery Questionnaire (PIQ) | 10  5 | X  X | X | X |
| **Schemas** | BCSS | 2 | X | X | X |
| **Trauma** | TALE | 5 | X |  |  |
|  | ITQ | 5 | X | X | X |
|  | BES | 5 | X | X | X |
| **Mental Health and Functioning** | BAI | 5 | X | X | X |
|  | CDS | 9 | X | X | X |
|  | WEMWBS | 5 | X | X | X |
|  | PSP | 10 | X | X | X |
| **Health Economics** | EQ-5D-5L | 2 | X | X | X |
|  | ReQoL-10 | 2 | X | X | X |
|  | Economic Patient Questionnaire | 10 | X | X | X |
|  |  |  |  |  |  |
| **Working Alliance** | WAI-client | 5 | 3^rd^ Session | 6^th^ | 9^th^ |
|  |  | 5 |  |  |  |
| **THERAPIST ONLY** | WAI-therapist | 5 | 3^rd^ Session | 6^th^ | 9^th^ |
|  | iMAPS therapy fidelity Checklist  CTS-R or CTS-Psy |  | A selection of therapy sessions will rated in supervision and by an independent external therapist |  |  |
| **Adverse Effects** | CGI-IP | 1 | Each Session |  |  |
|  | CGI-SP | 1 | Each Session |  |  |

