## ANALYSIS METHODS

**Quantitative analysis**

The analysis will follow the intention-to-treat (ITT) principle. Clinical outcome data will be sought and all available data included in the analyses regardless of adherence to the intervention during the time scale of the trial. Participants will be retained and analysed in their allocated arm. The CONSORT 2010 extension for reporting pilot and feasibility studies will be followed.

As this is a feasibility study the analysis will be mainly descriptive and focus on confidence interval estimation rather than hypothesis testing.

A statistical analysis plan (SAP) will be presented to and agreed with the programme steering group prior to the allocation codes being revealed and commencement of any data analysis. [name], with support from [name], (University of Manchester) will undertake the analysis of the trial data in line with the SAP which will be approved by the Trial Steering Committee prior to any analysis being performed.

The number of participants screened, eligible, consented, randomised and withdrawn from the study will be summarised and reported in a CONSORT flow diagram (Schulz, et al., 2010).

Demographic and other baseline characteristics will be summarised by randomised groups. Summary measures for the baseline characteristics of each group will be presented as mean and standard deviations and/or median and interquartile range (as appropriate), and as frequencies and percentages for categorical variables.

Key feasibility outcomes; recruitment rates, retention at the end of trial therapy and adherence to therapy (defined as the proportion of participants that attend at least 5 sessions) to assess the progression criteria to conduct a definitive trial will be presented as point estimates with 95% confidence intervals (using exact binomial methods).

Other feasibility outcomes such as unblinding rates, number and proportion of therapy sessions attended or cancelled, or the proportion of participants withdrawing from therapy will be summarised and reported in the same fashion.

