## Adherence and protocol deviations

### Adherence

Adherence to the intervention relies upon both therapist and participant factors.

a) Participant adherence

Participant adherence to the iMAPS-2 intervention will be measured by the number of therapy sessions attended by the participants allocated to the intervention arm. An individual will be classed as having attended a session if they attended a part or the whole of a session (defined as a minimum duration of 15 minutes). We will report the mean (SD) number of sessions attended or median (IQR), as appropriate. We will also summarise the number (%) of adherent participants with a 95% exact (binomial) confidence interval (for the %). If a participant attends 5 or more of the 12 sessions [4], then they will be deemed adherent.

b) Therapist fidelity

Therapist fidelity will be assessed by:

i) Rating a sample of audio recordings of therapy sess ions using the Cognitive Therapy Rating Scale Revised (CTS-R) or the Cognitive Therapy Rating Scale for Psychosis (CTS-Psy). Scale scores will be summarised as mean (SD) if they are (approximately) symmetrically distributed or median (IQR) if they are asymmetrically distributed.

ii) Therapists who are part of the research team (approximately 4 therapists) will complete the iMAPS fidelity scale after each therapy session to record the contents of each session in terms of: agenda targets; between-session activities/home tasks; the techniques used. Items within each domain of the fidelity scale will be summarised as follows:

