## Analysis populations

Feasibility analyses will include all the consented participants to estimate the proportion of eligible consented participants and eligible participants randomised. To summarise the number of iMAPS-2 therapy sessions attended, we shall include all the participants allocated to the intervention group. The proportion of adherent participants (attending at least 3 sessions of the iMAPS-2 therapy) will include all the participants allocated to the intervention group.

Analyses of efficacy will be by intention-to-treat (ITT), where all randomised participants for whom outcomes are available will be analysed in their allocated group regardless of their adherence to therapy.

The safety population will also follow the ITT principle and it will comprise all randomised participants.

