**Analysis**

Assessment of participant’s adherence and therapist fidelity are fully described in section 5.2.1.

The proportion of participants allocated to the intervention arm, attending at least 5 sessions of the iMAPS-2 therapy will be presented as point estimates with 95% (exact binomial) confidence intervals to assess the progression criteria to conduct a definitive trial.

In addition, we will report the proportion of participants whom have received at least 5 hours (300 minutes) of the iMAPS-2 therapy along with a 95% (exact binomial) CI. We will also summarise, as mean(SD) or median(IQR) as appropriate, the overall hours of iMAPS-2 therapy received, and the hours of iMAPS-2 therapy received by the adherent participants (those who received at least 5 sessions).

Finally, we will plot:

- A histogram showing the distribution of iMAPS-2 therapy sessions attended (whether they are part or whole sessions).
- A histogram showing the distribution of hours of iMAPS-2 therapy sessions attended.

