**Progression criteria**

Progression criteria for participant adherence is:

- Green (progress to full trial). At least 75% of the participants allocated to the intervention arm attend at least 5 sessions of iMAPS-2 therapy.
- Amber (full trial considered feasible if reasons for poor participant’s adherence identified and can be addressed). 40% - <75% of the participants allocated to the intervention arm attend at least 5 sessions of iMAPS-2 therapy.
- Red (unlikely to progress to full trial. Substantial amendments will be necessary to make a full trial feasible). If less than 40% of the participants allocated to the intervention arm attend at least 5 sessions of iMAPS-2 therapy.

**Objective 3.** What completion and data quality rates can be achieved (data completion and retention of participants)?

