**Supplementary Figure 1: Distribution of the number of therapy sessions attended and their duration in minutes**

The proportion of participants who began therapy and received at least 300 minutes (5 hours) of the iMAPS therapy was 23/29 (79%; 95%CI - 55% to 88%), with a mean (SD) and median of 495 (228) and 581 (350 to 660) of therapy minutes received respectively

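### SHEAP section 5.3 sets adherence at 3 sessions where every other statement sets 5, and the reported 300-minute result pairs an estimate on 29 participants with an interval on 31

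*Combined protocol and SAP*

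**What the plan says.** **Adherence threshold.** SHEAP section 5.3 (Analysis populations) puts adherence at 3 sessions: "The proportion of adherent participants (attending at least 3 sessions of the iMAPS-2 therapy) will include all the participants allocated to the intervention group". Five other statements put it at 5:

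- SHEAP section 5.2, Adherence: "If a participant attends 5 or more of the 12 sessions [4], then they will be deemed adherent".
- SHEAP section 7.2, Objective 2, Analysis: "The proportion of participants allocated to the intervention arm, attending at least 5 sessions of the iMAPS-2 therapy will be presented as point estimates".
- SHEAP section 7.2, Objective 2, Progression criteria (green): "At least 75% of the participants allocated to the intervention arm attend at least 5 sessions of iMAPS-2 therapy". The amber and red bands also use 5 sessions.
- Protocol section 3.11, Full Trial Progression Criteria: "GREEN>=75% adherence of participants attend at least 5 sessions of therapy".
- Protocol section 3.22, Analysis Methods: "adherence to therapy (defined as the proportion of participants that attend at least 5 sessions".

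**Time in therapy.** After the session-based measure, SHEAP section 7.2 adds a second descriptive proportion, those who "received at least 5 hours (300 minutes) of the iMAPS-2 therapy along with a 95% (exact binomial) CI". It names no denominator for it. The supplement limits the result to participants who began therapy and says that the proportion who "received at least 300 minutes (5 hours) of the iMAPS therapy was 23/29 (79%; 95%CI - 55% to 88" per cent. Supplementary Tables 2 and 10 give 31 participants in the iMAPS+TAU arm.

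**The concern.** Adherence is one of three progression criteria for the definitive trial. Section 5.3 tells the analyst who enters each proportion, so a different threshold there is an instruction that could be followed. Anyone who attends 5 sessions has also attended 3, so a 3-session count can only equal or exceed the 5-session count. Any error from following section 5.3 would be in the favourable direction.

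The 300-minute figure is the companion description of how much therapy people received, and planners of the definitive trial are likely to use it. As printed, the estimate and its interval cannot both come from the same data. The estimate leaves out 31 − 29 = 2 allocated participants, while the interval appears to include them.

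**Working it through.** **1. Threshold: the statements side by side.**

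| Place | Threshold | Denominator stated |
|---|---|---|
| SHEAP 5.3 | 3 | all allocated to intervention |
| SHEAP 5.2 | 5 of 12 | participants allocated to intervention (for sessions attended) |
| SHEAP 7.2, Objective 2 analysis | 5 | allocated to intervention |
| SHEAP 7.2, Objective 2 progression bands | 5 | allocated to intervention |
| Protocol 3.11 progression criteria | 5 | participants (not further specified) |
| Protocol 3.22 analysis methods | 5 | participants (not further specified) |

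Section 5.3 is the only outlier. It attaches no percentage and no traffic-light band to the 3 sessions. SHEAP 7.2 also sends the reader to section 5.2.1 for the full description of adherence, which is the 5-session definition.

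With 31 allocated, each participant who stopped at session 3 or 4 would add 1/31 = 3.2 percentage points under the 3-session wording. How many such participants there were cannot be found: the readable text gives no count attending at least 3 or at least 5 sessions.

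**2. The 300-minute interval.** Inputs: x = 23 and n = 29 from the text under Supplementary Figure 1; n = 31 from Supplementary Tables 2 and 10; exact binomial method from SHEAP 7.2.

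The exact (Clopper-Pearson) limits are

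- lower = the 0.025 quantile of Beta(x, n − x + 1)
- upper = the 0.975 quantile of Beta(x + 1, n − x)

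As a check on the method, 45/45 gives 92.1% to 100%, matching the 92% to 100% printed in the supplement for recruitment.

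The printed point estimate reproduces: 23/29 = 79.3%. The printed interval does not:

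| Proportion | Estimate | Beta distributions (lower; upper) | Exact 95% CI |
|---|---|---|---|
| 23/29 | 79.3% | Beta(23, 7); Beta(24, 6) | 60.3% to 92.0% |
| 23/31 | 74.2% | Beta(23, 9); Beta(24, 8) | 55.4% to 88.1% |
| Printed | 79% | | 55% to 88% |

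A different interval method does not explain it: for 23/29 the Wilson interval is 62% to 90% and the Wald interval 65% to 94%. Among all x/n with n from 25 to 45, 23/31 is the only pair whose exact interval rounds to 55% to 88%.

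**3. Size of the mismatch.** 79.3% − 74.2% = 5.1 percentage points in the estimate. For 23/29, the printed lower limit is about 5 points too low (55% against 60%) and the upper limit about 4 points too low (88% against 92%).

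**The case against.** The strongest reply is that the documents already settle which definition governs. The progression bands are written only with 5 sessions, SHEAP 7.2 points to section 5.2.1 for adherence, and the 3 sits in a parenthesis within a sentence about the denominator. An analyst weighing five statements against one would use 5. This stands as to consequence. A reader might infer that the adherence verdict depends on which line is followed, or that a 3-session rule makes green easier to reach. The documents do not support that: they contain no traffic-light rule based on 3 sessions, and without the counts no shift between bands can be shown. The contradiction still needs removing, because section 5.3 is an operative section and nothing in the plan gives another section precedence.

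A second reply is that the 300-minute measure is an addition, not a criterion, and that the plan names no denominator for it. Both parts stand. A reader might note that 74% and 79% fall on either side of 75% and infer that the choice of denominator decides the verdict. It does not, because the 75% cut applies to sessions attended, not minutes. Nor can the figure on 29 be called a departure from the plan: section 5.3 fixes the all-allocated denominator for sessions attended and session adherence, but does not mention minutes, and the supplement labels its group openly. What remains is narrower and certain: the estimate and interval printed together use different denominators.

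**Conclusion.** Two errors hold. SHEAP section 5.3 contradicts the 5-session definition used everywhere else in the protocol and SHEAP. The 300-minute result pairs 23/29 = 79% with the exact interval for 23/31. On one denominator it is either 74% (55% to 88%) over all 31 allocated or 79% (60% to 92%) over the 29 who began therapy.

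No change in the progression verdict is shown. Attributing the printed interval to 31 rests on taking the stated exact method and a numerator of 23 as correct; the unique match to 23/31, together with an arm size of 31, makes that reading firm. The severity is minor to moderate: a wording error in an operative section and a wrong interval in a reported descriptive result.

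**What to change.** 1. In SHEAP section 5.3, change the parenthesis to at least 5 sessions, so that it agrees with section 5.2, section 7.2 and the protocol. Record it as a correction of wording.
2. Confirm in the report that the adherence result used for progression counted at least 5 sessions over all 31 allocated to iMAPS+TAU.
3. Give the 300-minute proportion on one labelled denominator. The better choice is 23/31 (74%; 95% CI 55% to 88%), because it matches the all-allocated denominator used for session adherence. The result among those who began therapy, 23/29 (79%; 95% CI 60% to 92%), can stay as a labelled secondary.

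The cost is two line edits and one confirmation, with no new data. The downside is that the main 300-minute figure becomes about 5 points less favourable.

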# Trial Population

## Screening data

We will produce a CONSORT flow diagram [5]. The upper section of the CONSORT flow chart will include;

- Number of patients referred to the study.
- Number of patients screened.
- Number of potentially eligible patients contacted
- Number of patients recruited (i.e., consented)
- Number of participants recruited but not eligible, along with reasons for exclusions.
- Number of eligible participants.
- Number of eligible participants not recruited, along with reasons for non-recruitment.

## Eligibility

The number of non-eligible participants excluded due to not meeting the inclusion/exclusion criteria will be reported in the CONSORT flow chart as stated in section 6.1.

## Recruitment

The lower section of the CONSORT diagram [5] will be used to describe the course of participants through the trial. This will include the:

- Number of participants recruited
- Number of participants recruited but not randomised, included reasons for non-randomisation.
- Number of participants randomised.
- Number of participants allocated to each arm receiving their allocated intervention, and, for the intervention arm, the average number of sessions received.
- Number of participants not fully completing the trial, along with reasons for withdrawal from treatment, withdrawal from follow-up and loss to follow-up (without formal withdrawal from follow-up).
- Number of participants continuing through the trial and,
- Number participants included in the analyses.

We will present overall monthly figures of participants randomised, that will also be tabulated by randomised group.

## Withdrawal/follow-up

We will produce summaries by randomised group of the:

- Number (%) of participants withdrawing from the allocated intervention, along with reasons (if available).
- Number (%) of participants withdrawing fully from the trial (including all follow-up), along with reasons (if available).
- Number (%) of participants lost to follow-up (excluding those who formally withdrew from the trial).

## Baseline patient characteristics

We will summarise the following demographic characteristics both overall and by randomised group:

- Gender (Male/Female/Non-binary/Other)
- Age (years)
- Chart Diagnosis (ICD-11) Schizophrenia, Schizoaffective disorder, delusional disorder, Schizophreniform disorder, Unspecified (non-affective) psychosis – FEP, other.
- ICD-11 Code
- Illness severity as measured by the positive and negative syndrome scale (PANSS), (Mildly ill/Moderately ill/ Markedly ill/ Severely ill)
- Highest education level (Primary school/secondary school/Further education (e.g. College)/Higher education (e.g. University)
- Employment status (Full Time/Part Time/Retired/Voluntary/Student/ Home duties/ Unemployed)
- Marital status (Single/Married/Living with partner/Civil Partnership/Separated/ Divorced/Widowed)
- Living arrangements. Who does the person live with? (Spouse/Partner only, Spouse/Partner plus children, Spouse/Partner plus other/s (not children), Alone, Children only, Parent/s only, Friend/s only, Supported accommodation/hostel, Other)
- Index of Multiple Deprivation (IMD) Decile (derived from Postcode) (adjacent categories will be merged to form three broader categories: 1-3; 4-7; 8-10)
- Ethnicity (Bangladeshi/Indian/Pakistani/Any other Asian background/African/Caribbean/ Any other Black background/ White & Asian/White & Black African/ White & Black Caribbean/ Any other mixed background/ British/ Irish/Any other White background/ Chinese/Any other ethnic group/ Prefer not to answer)
- Treatments received (i.e. past therapy) and current treatment.
- Service type (Early Intervention Psychosis Team, CMHT, Inpatient)
- Inpatient/Outpatient status and legal status will also be reported
- BAI-rated Anxiety (minimal anxiety (0-7), mild anxiety (8-15), moderate anxiety (16-25), severe anxiety (26-63),).
- CDSS rated depression (minimal or absent (0-6), possible major depressive episode(7-27))

Summary measures for the baseline characteristics of each group and overall will be presented as mean and standard deviation, and median and interquartile range (IQR) for continuous variables, and frequency and percentage for categorical variables.

The categories for some of the variables such as ‘Living arrangements’ or ‘ethnicity’ might need to be merged at the time of analysis given the large number of categories and relatively small sample size.

The presence of traumatic events in each randomised group, as measured by the Trauma and Life Events (TALE) Checklist, will be summarised by frequency and percentage and tabulated by:

- Trauma type (item number): war exposure (1) / attachment-related (2 to 4) / witnessed verbal or physical abuse at home (9) / any interpersonal [bullying and discrimination (5&6), sexual abuse (13&14), emotional abuse (7) physical abuse (8&10), emotional neglect (11), physical neglect (12) ] / psychosis-related (15 to 17) / criminal justice (18) / non-interpersonal (19) / other trauma (20).
- Multiple exposure: Repeated events (at least 1 item answered ‘yes’ to ‘more than once’) / Multiple trauma types (more than 1 type of events reported)
- Trauma timing: Child (any time <age 16 years) / Adult (any time >age 16 years) / Both (any time <age 16 years AND > age 16 years).

The perceived impact and number of trauma types will be summarised by mean and standard deviation or median and interquartile range (IQR), as appropriate.

# Analysis

The results of the analyses will adhere to the CONSORT 2010 guidelines and its extension for reporting pilot and feasibility studies [5] [6].

## Calculation of clinical scores

This section describes the scoring and item non-response rules for each tool.

In the absence of tool-specific guidance on handling item non-response, we will seek to impute missing items to complete the tools. We will use a pragmatic approach where if no more than 35% of the items within a (sub)scale are missing, they will be imputed using the mean for all the completed items to provide a valid score for the (sub)scale total, otherwise the (sub)scale will be deemed missing. Total scores will only be available if there are valid (i.e. non-missing) scores for all subscales.

A 35% cut off will allow the scales with a small number of items to have 1 item missing, and the scales with larger number of items a relatively small % of missing items without biasing the results. In psychological outcomes, a range between 20% and 50% is considered acceptable.

